# Cosmesis and body image after single-port laparoscopic or conventional laparoscopic cholecystectomy: *a multicenter double blinded randomised controlled trial (SPOCC-trial)*

**DOI:** 10.1186/1471-2482-11-24

**Published:** 2011-09-12

## Abstract

**Background:**

Emerging attempts have been made to reduce operative trauma and improve cosmetic results of laparoscopic cholecystectomy. There is a trend towards minimizing the number of incisions such as natural transluminal endoscopic surgery (NOTES) and single-port laparoscopic cholecystectomy (SPLC). Many retrospective case series propose excellent cosmesis and reduced pain in SPLC. As the latter has been confirmed in a randomized controlled trial, patient's satisfaction on cosmesis is still controversially debated.

**Methods/Design:**

The SPOCC trial is a prospective, multi-center, double blinded, randomized controlled study comparing SPLC with 4-port conventional laparoscopic cholecystectomy (4PLC) in elective surgery. The hypothesis and primary objective is that patients undergoing SPLC will have a better outcome in cosmesis and body image 12 weeks after surgery. This primary endpoint is assessed using a validated 8-item multiple choice type questionnaire on cosmesis and body image. The secondary endpoint has three entities: the quality of life 12 weeks after surgery assessed by the validated Short-Form-36 Health Survey questionnaire, postoperative pain assessed by a visual analogue scale and the use of analgesics. Operative time, surgeon's experience with SPLC and 4PLC, use of additional ports, conversion to 4PLC or open cholecystectomy, length of stay, costs, time of work as well as intra- and postoperative complications are further aspects of the secondary endpoint. Patients are randomly assigned either to SPLC or to 4PLC. Patients as well as treating physicians, nurses and assessors are blinded until the 7th postoperative day. Sample size calculation performed by estimating a difference of cosmesis of 20% (alpha = 0.05 and beta = 0.90, drop out rate of 10%) resulted in a number of 55 randomized patients per arm.

**Discussion:**

The SPOCC-trial is a prospective, multi-center, double-blind, randomized controlled study to assess cosmesis and body image after SPLC.

**Trial registration:**

(clinicaltrial.gov): NCT 01278472

## Background

Since the first laparoscopic cholecystectomy in 1985, the laparoscopic approach has emerged as the treatment of choice for symptomatic gallstone disease [1,2]. Advantages of laparoscopic compared with open surgery include improved cosmesis, pain control, shorter convalescence and the absence of the formation of intra-abdominal adhesions.

Traditionally laparoscopic cholecystectomy is performed with four ports. In an attempt to further reduce operative trauma and improve cosmetic results following laparoscopic cholecystectomy, there has been a trend toward minimizing the number of incisions and ports required. These new operative techniques are called natural orifice transluminal endoscopic surgery (NOTES) [3,4] or single-port laparoscopic surgery (SPLC) [5] and were developed in order to improve cosmesis and further reduce the invasiveness of conventional laparoscopy [6].

A MEDLINE (Pubmed Central database) search (May 14, 2011) using the keywords 'cholecystectomy' and 'single port', 'single incision', 'single site' or 'single provided 334 articles. However, there were only two randomized controlled studies which were published. These included a low number of patients and focused on postoperative pain [7,8]. Current data show that SPLC is feasible with a low rate of conversion to 4-Port conventional laparoscopic cholecystectomy (4PLC) ranging from 2 to 9.3%. The main reason for conversion was the presence of acute inflammation [9,10]. Systemic reviews showed an incidence of biliary tract injury between 0.09 and 0.7%. [9-11]. However, high evidence regarding safety of SPLC is missing.

SPLC is regarded to provide excellent results in cosmesis with almost no visible scar [12,13]. Yet, the importance of the cosmesis has been challenged as patients also seem to be quite satisfied after 4PLC [14].

Since the available devices for SPLC have been designed to enable an almost scarless procedure the hypothesis of cosmesis improvement has to be proven. No previously published RCT on this topic was designed with the focus on cosmesis. We therefore designed a double-blinded randomized controlled trial on SPLC versus 4PLC (SPOCC-trial) evaluating cosmesis and body image as a primary endpoint.

## Methods/Design

### Study objectives

The SPOCC trial is a prospective, multi-center, double blinded, randomized controlled study comparing Single-Port laparoscopic cholecystectomy with 4-port conventional laparoscopic cholecystectomy in elective surgery for symptomatic cholecystolithiasis. Patients with an indication for an elective cholecystectomy are randomized for either (A) single-port laparoscopic cholecystectomy (SPLC) or (B) conventional 4-port laparoscopic cholecystectomy (4PLC). The hypothesis of this trial is that patients undergoing SPLC will have a better outcome in cosmesis and body image 12 weeks after surgery.

### Endpoints

The primary endpoint of the study concerns patient's satisfaction with cosmesis and body image 12 weeks after surgery. This endpoint is assessed using a validated cosmesis and body image score (CBIS) that was previously used in surgery for Crohn's disease [15] and in donor nephrectomy [16]. This score is calculated on an 8-item multiple-choice type questionnaire (Table 1) ranging between 8 and 48 points.

**Table 1 T1:** Cosmesis and Body image questionnaire consisting of a body image score (items 1 to 5) and a cosmetic score (items 6 to 8)

1	Are you less satisfied with your body since the operation? □ 1 = no, not at all □ 2 = a little bit □ 3 = quite a bit □ 4 = yes, extremely
2	Do you think the operation has damaged your body? □ 1 = no, not at all □ 2 = a little bit □ 3 = quite a bit □ 4 = yes, extremely
3	Do you fell less attractive as a result of your operation? □ 1 = no, not at all □ 2 = a little bit □ 3 = quite a bit □ 4 = yes, extremely
4	Do you feel less feminine/masculine as a result of your operation? □ 1 = no, not at all □ 2 = a little bit □ 3 = quite a bit □ 4 = yes, extremely
5	Is it difficult to look at yourself naked? □ 1 = no, not at all □ 2 = a little bit □ 3 = quite a bit □ 4 = yes, extremely
6	On a scale from 1 to 7, how satisfied are you with your scar(s)? □ 1 = very unsatisfied □ 2 = quite unsatisfied □ 3 = a bit unsatisfied □ 4 = not unsatisfied/not satisfied □ 5 = a bit satisfied □ 6 = quite satisfied □ 7 = very satisfied
7	On a scale from 1 to 7, how would you describe your scar(s)? □ 1 = revolting □ 2 = quite revolting □ 3 = a bit revolting □ 4 = not revolting/not beautiful □ 5 = a bit beautiful □ 6 = quite beautiful □ 7 = very beautiful
8	Could you score your own scar(s) on a scale from 1 to 10? (1 = ugliest scar imaginable, 10 = almost scarless)

Scores from 8 to 48.

The secondary endpoint is a combination of several variables: the quality of life 12 weeks after surgery assessed by the validated Short-Form-36 Health Survey questionnaire [17], postoperative pain assessed by a visual analogue scale daily assessment and the use of analgesics. Operative time, use of additional ports, conversion to open cholecystectomy, length of stay, costs, elapsed time before going back to work as well as intra- and postoperative complications represent aspects of the secondary endpoint. The postoperative complications are classified according to the Clavien-Dindo system [18].

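### The two parts of the primary score are coded in opposite directions, and the article states neither a reversal of items 1-5 nor which direction of the total is favourable

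*Protocol article*

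**What the plan says.** The Endpoints section of the protocol article makes satisfaction with cosmesis and body image at 12 weeks the primary endpoint and defines one total for it: "This score is calculated on an 8-item multiple-choice type questionnaire (Table 1) ranging between 8 and 48 points". Table 1 prints the eight items with their codes, and its footnote repeats the range: "Scores from 8 to 48". The table title assigns items 1-5 to a body image score and items 6-8 to a cosmetic score.

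- **Items 1-5** are worded as harm. The first is "Are you less satisfied with your body since the operation". All five use the same four codes, as in "Is it difficult to look at yourself naked? □ 1 = no, not at all", rising to 4 for the most extreme harm.
- **Items 6 and 7** run the other way, from 1 to 7: "how satisfied are you with your scar(s)? □ 1 = very unsatisfied" and "how would you describe your scar(s)? □ 1 = revolting", with 7 the most favourable answer.
- **Item 8** is also favourable at the top: "1 = ugliest scar imaginable, 10 = almost scarless".

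Power of the study defines a relevant improvement of the CBIS as 20%, given as 8 points, with an SD of 4 to 6 and 49 patients per group. Study objectives states the hypothesis that the single-port arm does better on cosmesis and body image. No section mentions recoding of items 1-5 or says whether a high total is favourable.

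**The concern.** The article goes well beyond naming the instrument. It prints every response code, the two parts, a combined total and its range, and then powers the trial on an improvement in that total. Someone programming the score from these pages would add the eight printed codes. Because the two parts point in opposite directions, that sum is not a scale from bad to good: a low body-image sum and a high scar sum are both good news.

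The hypothesis expects benefit on both parts, which is the case in which an unreversed sum offsets one against the other. If the parts move by different amounts, the sign of the arm difference shows only which part moved more, not which arm did better. Leaving the direction unstated also leaves a scoring choice on the primary endpoint open until data are in hand.

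**Working it through.** **Inputs.** Item codes and the 8-48 range: Endpoints and Table 1. The 8-point improvement, SD 4 to 6, two-sided alpha 0.05 and 49 per group: Power of the study.

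**1. The stated range.**
- Minimum: 5 × 1 + 1 + 1 + 1 = 8, which agrees with the article.
- Maximum: 5 × 4 + 7 + 7 + 10 = 44, not 48.
- Reversing items 1-5 (5 minus code) leaves each at 1 to 4, so the range is 8 to 44 either way. The printed range therefore cannot show which scoring was meant.

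**2. What the ends of the scale mean.**

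| Patient | Printed codes summed | Items 1-5 reversed |
|---|---|---|
| Best body image, best scars | 5 + 24 = 29 | 20 + 24 = 44 |
| Worst body image, worst scars | 20 + 3 = 23 | 5 + 3 = 8 |
| Best body image, worst scars | 5 + 3 = 8 | 20 + 3 = 23 |
| Worst body image, best scars | 20 + 24 = 44 | 5 + 24 = 29 |

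With printed codes, the worst-to-best span is 29 - 23 = 6 points, and the extremes belong to patients whose two parts disagree. With reversal, the span is 44 - 8 = 36 points and higher is always better.

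**3. Against the 8-point improvement.** Moving from the worst to the best answer on every item shows as 6 points on the unreversed sum, so improvement across the whole questionnaire cannot show as 8. A rise of 8 can arise only if the scar gain exceeds the body-image gain by 8.

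**4. Effect on the arm difference.** Let the single-port arm gain b points on body image and c on scars. The reversed total moves by b + c and the unreversed total by c - b. Approximate power in the favourable direction is Φ(Δ / (SD × √(2/49)) - 1.96), with √(2/49) = 0.202. For a true combined gain of 8:

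| b | c | Unreversed difference | Power, SD 4 | Power, SD 6 |
|---|---|---|---|---|
| 0 | 8 | 8 | about 1.00 | about 1.00 |
| 2 | 6 | 4 | 0.999 | 0.91 |
| 3 | 5 | 2 | 0.70 | 0.38 |
| 4 | 4 | 0 | no effect to detect | no effect to detect |
| 8 | 0 | -8 | wrong sign | wrong sign |

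Example, b = 3, c = 5, SD 6: 2 / (6 × 0.202) = 1.65; 1.65 - 1.96 = -0.31; Φ(-0.31) = 0.38. On the reversed total every row is a difference of 8, with power close to 1.

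The splits are illustrative; the article gives no expected effect by part. The calculation also assumes that the quoted SD of 4 to 6 applies to the unreversed sum, which the article does not establish.

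**The case against.** The strongest reply is that the article is silent on reversal and does not exclude it. Table 1 shows the patient's form, and codes on a form are not a derivation rule. The Endpoints section calls the score validated and cites earlier uses, and the Discussion refers to an existing scoring system. Recoding of negatively worded items could well be specified there, or in a full protocol or analysis plan that is not shown.

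The article's own use of the score also suggests a directional total: 20% of 48 - 8 = 40 is 8 points, which fits a scale running about 40 points from worst to best and not a 6-point span. That link is inferred, since the article does not say what the 20% is taken of.

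Finally, the Background notes that patients seem fairly satisfied after the four-port operation. If so, body-image answers may sit near their floor, b would be small and little power would be lost.

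Much of this stands. A reader might infer that the trial adds the items unreversed and that its power collapses. The documents support neither: no section says that raw codes are summed, and the loss runs from negligible to total depending on b, for which no figure is given.

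The reply does not remove the point. The article chose to print a scoring definition, that definition misleads if followed as it stands, and the printed range cannot correct it, being the same under both scorings and wrong at its upper end. A claim of validation attaches to a particular scoring rule, and that rule is not stated here.

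**Conclusion.** The point holds as a defect in how the primary endpoint is fixed on paper. Table 1 codes the two parts in opposite directions, one total is formed from them, and neither a reversal nor the favourable direction is stated. These facts, and the values 29, 23, 8 and 44, follow from the printed codes without further assumption.

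The consequence is conditional. If the printed codes are summed, the worst-to-best span is 6 points, gains on the two parts offset each other, and the sign of the result can be wrong. If the cited scoring system reverses items 1-5 and the trial follows it, the analysis is unaffected and only the description needs repair. Confidence is therefore high on the gap in the text and moderate on any harm to the result. Because the primary endpoint is involved and the correction is very small, it should be made before the 12-week analysis.

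**What to change.** Add to the endpoint definition that items 1-5 are scored as 5 minus the recorded code before summing, that a higher total is better, and that the total runs from 8 (worst) to 44 (best) in place of 8 to 48. Confirm that this agrees with the cited scoring system. Program the derivation before any 12-week data are analysed.

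One knock-on needs a decision: over the attainable span of 36 points, 20% is 7.2, so the article should say what the 8-point threshold is a percentage of.

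Reporting the body image score (5 to 20) and the cosmetic score (3 to 24) beside the total would help interpretation but is optional. The cost is one sentence and one line of derivation code. No new data are needed.

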### Power of the study

A clinically relevant improvement of the cosmesis and body image score (CBIS) [15] is defined as an improvement of 20% of the cosmesis score (8 points). Given the reported standard deviation of the CBIS between 4-6 [19] and using (alpha = 0.05 and beta = 0.90), two groups of 49 patients are needed. This is based on a two-sided significance level (alpha) of 0.05 and a power of 0.90. Estimating a 10% dropout rate, which is common in randomized controlled trials [20], 55 patients will be randomized per arm.

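### The primary score is said to run to 48, but its printed items sum to at most 44, and on that scale 20% is not 8 points

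*Protocol article*

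**What the plan says.** The Endpoints section names patient satisfaction with cosmesis and body image at 12 weeks as the primary endpoint, measured by the CBIS. It describes the instrument thus: "This score is calculated on an 8-item multiple-choice type questionnaire (Table 1) ranging between 8 and 48 points". The note under Table 1 gives the range again: "Scores from 8 to 48".

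Table 1 prints the whole questionnaire, "consisting of a body image score (items 1 to 5) and a cosmetic score (items 6 to 8"). Items 1 to 5 each offer four answers, the last being "4 = yes, extremely". Item 6 opens "On a scale from 1 to 7, how satisfied are you with your scar(s") and item 7 opens "On a scale from 1 to 7, how would you describe your scar(s"). Item 8 asks for a mark from 1 to 10. The article describes no weighting, rescaling or other scoring rule.

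The Power of the study section says that a relevant improvement on the CBIS "is defined as an improvement of 20% of the cosmesis score (8 points"). It combines this with an SD of 4 to 6, a two-sided alpha of 0.05 and power of 0.90, and arrives at 49 patients per group, or 55 randomised per arm after 10% dropout. The Abstract gives the 20% without a point value.

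**The concern.** The instrument and its stated range appear together and disagree. Nobody can score 45 to 48 on the questionnaire as printed. This is the scale of the sole primary endpoint, and the relevant difference is expressed as a percentage as well as in points, so the width of the scale affects how the result is read.

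If the percentage and the point value are not the same quantity, the trial has more than one threshold for relevance. An observed difference of 7.5 points, for example, would exceed 20% of the printed width but fall short of 8 points. A reader of the Abstract, which gives only the percentage, could not tell which one applies.

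**Working it through.** **Inputs.** The item response ranges come from Table 1. The range 8 to 48 comes from the Endpoints text and the note under Table 1. The 8 points, 20%, SD of 4 to 6, alpha, power and 49 per group come from Power of the study.

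**Range of the printed score (unweighted sum)**

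- Minimum: 5×1 + 2×1 + 1 = 8, which agrees with the stated minimum and supports simple summation.
- Maximum: 5×4 + 2×7 + 10 = 20 + 14 + 10 = 44, which is 4 below the stated 48.
- Width: 44 − 8 = 36, against 48 − 8 = 40 as stated.
- Sub-scores: body image 5 to 20, cosmetic 3 to 24.
- Reverse-scoring items 1 to 5 changes none of this, because a reversed 1-to-4 item still runs from 1 to 4.

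**What 20% comes to**

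| Base | 20% of base |
|---|---|
| Stated width, 40 | 8.0 |
| Stated maximum, 48 | 9.6 |
| Printed width, 36 | 7.2 |
| Printed maximum, 44 | 8.8 |
| Cosmetic sub-score width, 21 | 4.2 |
| Cosmetic sub-score maximum, 24 | 4.8 |

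Of these bases only the width of the stated 8-to-48 range gives exactly 8. On the printed scale, 8 points is 8/36 = 22.2% of the width or 8/44 = 18.2% of the maximum.

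**Effect on sample size.** With the normal approximation, n per group = 2(1.960 + 1.282)² × (SD/difference)², or about 21.0 × (SD/difference)², rounded up. The exact t-test result is in brackets.

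| Difference | SD 4 | SD 5 | SD 6 |
|---|---|---|---|
| 8 points | 6 (7) | 9 (10) | 12 (13) |
| 7.2 points | 7 (8) | 11 (12) | 15 (16) |

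For example, at 8 points and SD 6: 21.0 × (6/8)² = 11.8, so 12. At 7.2 points and SD 6: 21.0 × (6/7.2)² = 14.6, so 15. With 49 per group and SD 6, power exceeds 99.9% for either difference.

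**The plan's own 49.** The stated inputs do not reproduce it. At 8 points and SD 4 to 6, one- or two-sided, normal or t-test, the results run from 5 to 13. Dividing the two-sided t-test n by 0.864, to allow for a Wilcoxon test, gives at most 16. A difference of 4 points with SD 6 does reproduce it: 21.0 × (6/4)² = 47.3, so 48, or 49 by t-test. For 8 points to need 49 per group, the SD would have to be about 12.2. The dropout step is right: 49/0.9 = 54.4, so 55.

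**The case against.** The strongest reply is that this is a labelling slip with almost no consequence for the design. The threshold is given in points, and an 8-point difference can be used whatever maximum is printed. Randomisation, the test and the analysis set do not depend on the maximum. Moving from 8 to 7.2 points raises the need to at most 16 per group by t-test, against 49 planned. All of this stands, and it limits the weight of the point. It does not remove the contradiction: the questionnaire is fully legible, 48 appears in two places, and the article prints both the items and the range, so neither condensation nor a damaged table explains the difference.

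Several stronger readings are tempting but not supported:

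- *The 8 points was derived from the wrong range.* A reader might infer this because 20% of 40 is 8. The article never says what the 20% is taken of, and 20% of a reference mean of 40 would also give 8, although no such mean is stated. The figures are consistent with that derivation but do not prove it.
- *A ceiling at 44 makes an 8-point gain unattainable.* That would need a control mean above 36, and it would need 44 to be the best score, which requires items 1 to 5 to be reverse-scored. The article states neither. Its Background remark that patients seem fairly content after the 4-port operation is qualitative and cannot place the mean.
- *The threshold belongs to the cosmetic sub-score.* The 4.2 and 4.8 points depend on this reading. The same paragraph speaks of improvement on the CBIS and uses the SD of the CBIS, so the phrase is more naturally loose shorthand for the total. Only an ambiguity of wording remains.
- *The data platform accepts impossible totals.* The article describes no range check, so there is nothing to correct.

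**Conclusion.** The stated maximum of 48 is wrong for the questionnaire as printed; the items give 8 to 44. This rests on one assumption, that the score is the plain sum of the items, which the stated minimum of 8 supports and nothing in the article contradicts. It follows that 20% and 8 points do not agree on either the width or the maximum of the printed scale: 20% is 7.2 or 8.8 points respectively, and 8 points is 22.2% of the width.

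The consequence is confined to the definition and reading of the primary endpoint and its relevance threshold. A reader might conclude that the trial is underpowered because of the range error, but the calculations show otherwise. That 8 points with an SD of 4 to 6 does not lead to 49 per group is a separate discrepancy in the power section. It matters here because restating the difference as 7.2 or 8.8 points would still leave that section irreproducible.

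**What to change.** 1. In the Endpoints text and the note under Table 1, correct the range to 8 to 44, with sub-scores 5 to 20 (body image) and 3 to 24 (cosmetic). If a scoring rule exists that yields 48, state it instead.
2. In Power of the study and the Abstract, give the relevant difference in points on the total CBIS, name the base of the percentage, and make the two agree. If 8 points is kept, that is 22.2% of the 36-point width; if 20% of the width is kept, that is 7.2 points. Use the name of the total score rather than a term that could mean items 6 to 8.
3. In the same revision, reconcile the chosen difference and SD with the 49 per group, and state the inputs that reproduce it.

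The first two steps cost a few text corrections. The third requires going back to the sample-size calculation that was run. Correcting the range does not by itself require more patients.

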### Power of the study

A clinically relevant improvement of the cosmesis and body image score (CBIS) [15] is defined as an improvement of 20% of the cosmesis score (8 points). Given the reported standard deviation of the CBIS between 4-6 [19] and using (alpha = 0.05 and beta = 0.90), two groups of 49 patients are needed. This is based on a two-sided significance level (alpha) of 0.05 and a power of 0.90. Estimating a 10% dropout rate, which is common in randomized controlled trials [20], 55 patients will be randomized per arm.

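### The stated inputs (8 CBIS points, SD 4 to 6, two-sided alpha 0.05, power 0.90) give 7 to 13 patients per arm, not the 49 said to be needed

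*Protocol article*

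**What the plan says.** The primary endpoint is the CBIS at 12 weeks, a total score described under Endpoints as "ranging between 8 and 48 points". Power of the study sets the clinically relevant improvement, which "is defined as an improvement of 20% of the cosmesis score (8 points"). The variability is introduced with "Given the reported standard deviation of the CBIS between 4-6"; the single value used in the calculation is not named. The result is that "two groups of 49 patients are needed", followed by "This is based on a two-sided significance level (alpha) of 0.05 and a power of 0.90". A 10% dropout allowance then leads to "55 patients will be randomized per arm".

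The Methods/Design paragraph of the abstract repeats the basis without points or an SD: "Sample size calculation performed by estimating a difference of cosmesis of 20% (alpha = 0.05 and beta = 0.90, drop out rate of 10"%), giving 55 randomised patients per arm.

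**The concern.** Eight points is at least 1.3 SD on the protocol's own figures (8/6 = 1.33; 8/4 = 2.0). Effects of that size need small groups, so 49 per arm looked several times too large for the inputs printed beside it.

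At stake is the only justification given for the size of the primary comparison. If 8 points and SD 4 to 6 are right, 110 patients are randomised where about 30 would meet the stated power. If 49 is right, the difference or the SD behind it is not the one printed. In either case a reader cannot tell what effect the trial was designed to detect, and a significant result could be well below the improvement that the protocol calls clinically relevant.

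**Working it through.** **Inputs.** From Power of the study: difference 8 points; SD 4 to 6; two-sided alpha 0.05; power 0.90; two equal groups; dropout 10%. From Endpoints: scale 8 to 48, span 40, so 20% of the span is 0.20 × 40 = 8. The 8 points therefore fit the total CBIS.

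**Step 1. The protocol's own figures.** The dropout step reproduces: 49 / (1 − 0.10) = 54.4, rounded up to 55. The 49 does not.

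**Step 2. Required size for 8 points.** Normal approximation: n per arm = 2 × SD² × (1.960 + 1.282)² / difference², with (1.960 + 1.282)² = 10.51. The t-test column uses the exact noncentral t distribution.

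| SD | Normal approximation | Rounded up | Exact t-test |
|---|---|---|---|
| 4 | 2 × 16 × 10.51 / 64 = 5.3 | 6 | 7 |
| 5 | 2 × 25 × 10.51 / 64 = 8.2 | 9 | 10 |
| 6 | 2 × 36 × 10.51 / 64 = 11.8 | 12 | 13 |

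After 10% dropout the largest of these is 13 / 0.9 = 14.4, so 15 per arm or 30 in all.

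**Step 3. Could another convention give 49?** With 8 points and SD 6:
- one-sided alpha gives 10 (normal approximation);
- power 0.80 gives 9 and power 0.95 gives 15 (normal approximation);
- a Wilcoxon test with worst-case efficiency gives 13 / 0.864 = 15.05, so 16;
- a change score with uncorrelated baseline (SD 6 × √2 = 8.5) gives 24 to 25.

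None comes near 49.

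**Step 4. What would give 49?**
- 4 points at SD 6: 2 × 36 × 10.51 / 16 = 47.3, so 48 by the normal approximation and exactly 49 by the t-test (power 0.904).
- 8 points at a larger SD: the t-test at 49 per arm detects 0.661 SD with 90% power, so SD = 8 / 0.661 = 12.1, twice the top of the stated range.

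**Step 5. What 49 per arm delivers.**
- Power for 8 points: at SD 6 the expected z is 8 / (6 × √(2/49)) = 8 / 1.212 = 6.60, which gives power 0.999998. It is higher still at SD 4 and 5.
- Difference detectable with 90% power (0.661 × SD): 2.6, 3.3 and 4.0 points at SD 4, 5 and 6.
- Smallest observed difference with p < 0.05, t(0.975; 96) × SD × √(2/49) = 1.985 × SD × 0.202: 1.6 points at SD 4 and 2.4 points at SD 6. As shares of 8 points these are 20% and 30%.

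**The case against.** **The error is on the safe side.** Power for 8 points is ample, type I error is untouched, and the dropout step is right. This stands. The effect, size and power are not mutually impossible, since 49 per arm does give at least 90% power for 8 points. What fails is the statement that 49 are needed.

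**Any powered trial can be significant below its design difference.** This also stands in part. With 13 per arm and SD 6 the threshold would be 2.064 × 6 × √(2/13) = 4.9 points, 61% of 8. At 49 per arm it falls to 30%. The change is one of degree, but a large one. Nor does the protocol claim that p < 0.05 would establish a 20% improvement; its hypothesis is only a better outcome.

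**A reader might infer that the trial was really sized for 4 points, half its relevant effect.** The exact match at SD 6 makes this tempting, but the document does not support it as fact. It mentions no 4-point difference and does not name the SD used. At SD 4 or 5 the same size targets 2.6 or 3.3 points, and 8 points with an SD of about 12 gives 49 as well.

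**A reader might also infer two further errors.** One is that the 20% was meant for the cosmetic sub-score, because the text says cosmesis score. But the sentence and the SD concern the CBIS, and 8 points is 20% of its stated span. The sub-score readings do not yield 49 either: 20% of the sub-score's span (3 to 24) is 4.2 points and 20% of its maximum is 4.8, which need 44 and 34 per arm at SD 6. The other is that beta = 0.90 signals a different calculation. It is a labelling slip, which the next sentence of Power of the study resolves by giving the power as 0.90; it changes no number.

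**Conclusion.** Wrong as written. The inputs printed in Power of the study lead to 7, 10 or 13 evaluable patients per arm, so 49 is about four to seven times too many (49/13 = 3.8; 49/7 = 7.0). The direction is over-sizing against the stated target, not a shortage of power. Which input is at fault cannot be settled from the document.

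The conclusion takes the SD range and the 8 to 48 scale as stated and assumes a two-group comparison of the 12-week score by t-test; the alternatives tried do not alter it. It does not depend on anything left to an unseen analysis plan, because the inputs and the result stand in the same paragraph and disagree.

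**What to change.** Keep 110 patients. In Power of the study:

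1. State the difference and the SD actually used, and reconcile them with 49 and 55 per arm.
2. If the sponsor cannot confirm them, say instead that 49 evaluable patients per arm give 90% power (two-sided alpha 0.05) for about 2.6 to 4.0 CBIS points at SD 4 to 6, and more than 99.9% power for 8 points. Do not adopt 4 points merely because it reproduces 49.
3. Say that the difference refers to the total CBIS.
4. Write power = 0.90 (beta = 0.10), here and in the abstract.
5. Add that the estimated difference will be read with its 95% CI against the 8-point relevance threshold.

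The cost is rewording one paragraph and one sentence of the abstract, and a less tidy justification. No patients, visits or analyses change.
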